## Methods

### Hypotheses and aims

We hypothesize that implementing a pharmacist-led medication review and provision of deprescribing recommendations to general practitioners (GP) will reduce the use of anticholinergic and sedative medications in community-dwelling older people compared to the control arm overall and that the reduction will be more pronounced for older people with a greater level of frailty. Thus, the primary objective is to determine if pharmacist-led medication reviews focused on reducing anticholinergic and sedative medications lead to GPs deprescribing these medications for older people living in the community. The secondary objective is to determine if a frailty measure based on data collected in the interRAI Home Care [24] and Contact assessment [25] can identify a group of older people who could benefit the most from deprescribing.

The interRAI is a comprehensive assessment database system utilized internationally and in New Zealand to standardize the evaluation of complex care needs of older people. It is routinely used to collect data regarding patients’ medical and functional status [26]. In New Zealand, the comprehensive Home Care assessment [24] is used for persons seeking admission into publicly funded aged residential care, while the shorter contact assessment [25] is for home-based support services. The reliability of the interRAI™ has been tested, and it has been shown to meet or exceed the standard cut-offs for acceptable reliability [27].

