Lorazepam	N05BA06	Zolpidem	N05CF02
Lormetazepam	N05CD06	Zuclopenthixol	N05AF05
Methadone	N07BC02		

After enrolment, participants will be stratified using a frailty index (FI), which will be based on a cumulative deficit model using 15 relevant items common to the interRAI Homecare and Contact assessments. Cut-off values for each stratum will create three equal-sized frailty strata based on New Zealand interRAI HC and CA data used for developing the frailty index. Participants will be stratified into one of three frailty strata (low, medium, high) and allocated in a 1:1 ratio within each strata to the intervention and control arms of the trial.

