#### Secondary outcomes

Secondary outcomes measures will be compared between the two arms of the trial after 6 months and are outlined in Table 3. From the funder’s perspective, these include the number of hospitalizations, emergency department visits, entry into aged residential care, all-cause mortality, and cost-utility. In addition, we will measure the number of emergency department visits and unplanned hospital admissions. Data on entry into or change in the level of care in aged residential care will be extracted from relevant national databases by the analytical services of the Ministry of Health. Patient mortality data will be matched using participants’ National Health Index (NHI) number, added to the dataset, and analyzed using competing risk regression. In a separate analysis, we will conduct a health cost utility assessment.

**Table 3 Tab3:** Outcome measures and analysis

Outcome	Measure	Alternative hypothesis	Analysis
Drug burden change	Proportion ΔDBI ≥ 0.5	Intervention greater	*χ*^2^ comparison of proportions
Emergency department visits	Proportion	Remain the same or decrease	*χ*^2^ comparison of proportions
Unplanned hospital admissions	Proportion	Remain the same or decrease	*χ*^2^ comparison of proportions
Admissions into aged residential care	HR	Remain the same or decrease	CRRA
Mortality	HR	Remain the same or decrease	CRRA

*ΔDBI* change in Drug Burden Index, *WSR* Wilcoxon signed-rank test, *CRRA* competing risk regression analyses, *χ*^2^ chi-square

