#### Statistical analysis

The data analysis will use the intention-to-treat principle (where all available data, including records showing non-adherence to the protocol, from participants will be included in the analysis). Thus, imputation will not be used for missing data.

We will compare the proportions of the outcome measures using a chi-squared test and present results with a 95% confidence interval.

We will present Kaplan-Meier survival curves for analysis of hospitalizations, emergency department visits, entry into aged residential care, and mortality within subgroups. Subgroups will include control low frailty, control medium frailty, control high frailty, intervention low frailty, intervention medium frailty, and intervention high frailty. The analyses will be controlled for age and sex, with death as a censored event. We will then conduct a competing risk analysis using cumulative incidence functions (CIF). For example, where entry to aged residential care is the primary event of interest, death is the competing event. The CIFs are the probability of observing these events before the end of the 6-month follow-up period.

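### The residential-care hazard ratio is not planned to use interRAI assessment type, a free baseline predictor; the loss is a little power, not bias

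*Protocol article*

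**What the plan says.** All references are to the protocol article.

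- **Adjustment.** Statistical analysis describes Kaplan-Meier curves and their subgroups, then says: "The analyses will be controlled for age and sex, with death as a censored event". The subgroups combine arm and frailty: "Subgroups will include control low frailty, control medium frailty, control high frailty, intervention low frailty, intervention medium frailty, and intervention high frailty". Cumulative incidence functions (CIFs) follow, over a 6-month horizon: "The CIFs are the probability of observing these events before the end of the 6-month follow-up period".
- **Outcome.** Table 3 (Secondary outcomes) has a row "Admissions into aged residential care", measured as a hazard ratio and analysed by competing-risk regression. No covariate list is attached to that regression.
- **Assessment type.** Hypotheses and aims says that "the comprehensive Home Care assessment [24] is used for persons seeking admission into publicly funded aged residential care". The same sentence gives the other form a different purpose, namely for people who want help at home: "while the shorter contact assessment [25] is for home-based support services". Under Participants, either assessment qualifies a person for the trial.
- **Randomisation.** Participants are put into three frailty strata and "allocated in a 1:1 ratio within each strata to the intervention and control arms of the trial". The frailty index uses "15 relevant items common to the interRAI Homecare and Contact assessments", so it does not contain assessment type itself. Assessment type is named nowhere as a stratum or covariate.

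**The concern.** By the article's own description, one of the two routes into the trial is the route taken by people who are looking to enter residential care. Entry to residential care is then compared between arms. Assessment type is therefore a plausible strong baseline predictor of this one outcome, and it is known for every participant from the interRAI assessment at T0. It is used neither in allocation nor in the stated adjustment.

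A hazard-ratio model that omits a strong predictor estimates a ratio somewhat nearer to 1 and has somewhat less power. Naming the factor in advance also avoids an after-the-fact decision to adjust if the arms turn out to differ on it.

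A smaller point concerns wording. The adjustment sentence directly follows the Kaplan-Meier description. Ordinary Kaplan-Meier curves and CIFs are not adjusted for covariates, and no weighting or standardisation is described. A reader cannot tell which analysis age and sex belong to.

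**Working it through.** **1. The plan's own figure.** The article gives no event count or power for residential-care entry; its stated size is for the proportion with a DBI reduction of at least 0.5. For 4% v 14%, 90% power and two-sided α = 0.05 (sidedness assumed):

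n = (1.960 + 1.282)² × (0.04×0.96 + 0.14×0.86) / 0.10² = 10.51 × 0.1588 / 0.01 = 166.9, so 167 per arm.

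This reproduces the stated 167. It supplies the arm size used below and is otherwise unaffected.

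**2. Assumed inputs (not in the article).** Half of participants assessed by Home Care. Six-month entry of 30% (Home Care) v 4% (Contact), with a range from 20% v 3% to 40% v 5%. Deaths 5% over 6 months.

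**3. Chance imbalance in assessment type.** Without stratification on it, and ignoring whatever frailty stratification absorbs:

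- SD of the arm difference in Home Care share = √(2×0.5×0.5/167) = 0.055; 95% range ±1.96×0.055 = ±10.7 points.
- Within one frailty stratum (56 per arm): √(2×0.25/56) = 0.094; ±18.5 points.

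**4. What an imbalance at the edge of that range does to an unadjusted hazard ratio when the true value is 1.** The cumulative hazards are −ln(0.96) = 0.041 and −ln(0.70) = 0.357. With Home Care shares of 55.4% and 44.6%:

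- arm A: 0.446×0.041 + 0.554×0.357 = 0.216
- arm B: 0.554×0.041 + 0.446×0.357 = 0.182
- ratio ≈ 1.19

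Over a wider set of assumptions (Home Care share 30-70%, entry 3-5% v 12-35%) the ratio is about 1.10 to 1.26. This is random error, which α and the confidence interval already cover.

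**5. What adjustment gains on the planned scale.** I simulated the trial (334 participants, 6 months, 4,000 replicates per setting) and fitted a cause-specific Cox model with arm alone, then with arm plus assessment type. Rejection is at two-sided 5%. The mean hazard ratio is the exponential of the mean log ratio.

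| Entry, Home Care v Contact | Null rejection, without / with | Power at true HR 0.5, without / with | Mean HR, without / with |
|---|---|---|---|
| 20% v 3% | 4.8% / 4.6% | 39.1% / 40.5% | 0.501 / 0.493 |
| 30% v 4% | 4.4% / 5.0% | 55.2% / 58.6% | 0.507 / 0.492 |
| 40% v 5% | 4.6% / 5.2% | 65.6% / 71.7% | 0.517 / 0.494 |

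The power gain is 1.4, 3.4 and 6.1 points (simulation error about 0.5 point). A subdistribution (Fine-Gray) version gives 1.4, 3.3 and 6.1 points. In a smaller simulation (400 replicates) over Home Care shares of 30-70% and entry of 12-35% v 3-5%, power changed by −1 to +4 points, the mean hazard ratio moved by at most about 0.02, and null rejection was about 2-6% either way.

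**6. A tempting figure that does not carry over.** On the risk-difference scale, assessment type would explain (0.0547×0.26)² / (2×0.17×0.83/167) = 0.000202/0.001690 = 12% of the variance of the arm difference (7% to 18% over the range). Table 3 plans a hazard ratio, where the benefit comes mainly as less attenuation, so 12% is not the precision gain for the planned analysis.

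**The case against.** The strongest case against is that nothing here is an error. In a 1:1 trial, choosing age and sex over another baseline covariate leaves the arm comparison valid. Frailty is the randomisation stratum and the subgroup basis of the curves; it comes from the same interRAI assessments and may absorb part of the difference between assessment types. The Home Care share and entry rates are assumed, and the exclusions for dementia, cognitive impairment and short life expectancy make them hard to guess. The outcome is secondary. The article is condensed, and a full protocol or analysis plan may list the regression covariates.

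Most of this stands, and it sets the severity. It does not remove the point: the article does name its controls, and the factor it leaves out is one that its own text links to this outcome.

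Three stronger readings might be inferred and are not supported:

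- **That the residential-care comparison is biased, or its type I error inflated.** Randomisation rules out systematic bias, and null rejection stays near 5% with or without the factor.
- **That age and sex are the only baseline factors used.** The sentence just before the quoted one brings in frailty.
- **That the mortality and hospital analyses need the same factor.** The rationale concerns seeking residential care, so it is specific to that outcome. Table 3 analyses emergency visits and unplanned admissions by chi-squared test, so it lists no hospital regression to stratify.

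On the curves, adjusted survival and incidence curves do exist, so the sentence is unclear rather than wrong.

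**Conclusion.** The point holds as a small, free improvement of low severity. The stated adjustment covers age and sex, with frailty as the subgroup basis, and leaves out interRAI assessment type for an outcome that the article itself connects to that assessment. The planned comparison remains valid.

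The loss is about 2 to 4 points of power near the middle of the assumed range at a true hazard ratio of 0.5, about 1 point at the low end and 6 at the high end, plus attenuation of the hazard ratio by about 0.01 to 0.02. These figures rest on half the participants being assessed by Home Care and on the assumed entry rates. They would be smaller if assessment type predicts entry less strongly, or if frailty carries part of the same information. The unclear target of the adjustment sentence is a matter of wording only.

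**What to change.** In Statistical analysis, and in the residential-care row of Table 3, prespecify the competing-risk regression for entry to residential care with interRAI assessment type (Home Care v Contact) as a stratum or covariate, alongside age, sex and the frailty stratum. Add one sentence saying that covariate adjustment applies to the regression and not to the Kaplan-Meier or CIF curves. Leave the mortality and hospital analyses as they are on this point.

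The cost is analysis wording and one variable already collected at T0. Sample size, randomisation and data collection do not change. If a full analysis plan already lists assessment type for this model, only the sentence about the curves is needed.

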#### Cost-benefit analysis

As a separate analysis, a health economist will oversee an analysis of financial costs of routine screening for frailty compared to the expected benefits from more appropriate prescribing, reduced pharmaceutical costs, and avoided hospital admissions and entry into residential care. Given that we will stratify our cohort by frailty, we anticipate identifying a group of participants with a degree of frailty who will benefit most from targeted medication reviews.

The cost-effectiveness analysis will include costs and benefits both for the participants and for the health care system. Standard robustness checks will be performed.

A desirable feature is that the benefits of implementing the intervention are likely to be realized soon after implementation, contributing to a favorable cost-effectiveness ratio [33].

#### Reporting and dissemination

The trial results will be disseminated to medical professionals and researchers via journal articles, to local health authorities and delivery organisations through presentations, newsletters and media interviews, and study participants who requested information on the study’s outcome via a simplified summary.

We will report according to the CONSORT reporting guidelines [34].

Authorship will be considered and granted using policies of the University of Otago [35] and respective journals. Funder and other contributors to the study or dissemination method will be acknowledged in the publication.

Disclosure of participant-level data is not consented to and will therefore not be made available.

### Blinding

Participants will be blinded to their study arm. The pharmacists conducting the first medication reviews will be blinded at the time of the medication review but made aware of allocation following the review when they open the envelopes at the first home visit. Pharmacists conducting post-intervention medication reviews will be blinded to the participants’ allocation in the follow-up home visits. Therefore, those pharmacists collecting medication data at either step will be blinded. Data collected for other outcome measures are collected independent of the study; thus, blinding is ensured. Patient unblinding is permitted in case of health concerns requiring immediate attention.

The study administrator and the data manager will have access to all participant data. The primary investigator and the study statistician will be blinded to participant data and allocation during the trial and unblinded following data verification and locking.

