#### Intervention arm

In the intervention arm of the trial, pharmacists will discuss with participants the medical conditions with which the DBI medications have been prescribed and their experiences with these medications. The consultation will determine if the potential harm of DBI medications prescribed outweigh their possible benefits. The participant and their family’s beliefs about the continued need for these medications and their preferences regarding willingness to discontinue these medications will also be determined via the consultation. After the consultation, target anticholinergic/sedative medications will be documented along with the participant’s concerns regarding these medications. Study pharmacists will consider the participants’ medical history as conveyed by the participants, their interRAI assessments, and their electronic medication records, if available.

The deprescribing implementation strategy that will be employed will focus on reducing or stopping anticholinergic and sedative medications to reduce participants’ DBI scores, using a process that was adapted from [2] and previously trialled in a New Zealand residential aged care setting [28, 29]. The process used in this study will differ from that used in the above residential care study because our study pharmacists will not have access to prescribing lists and clinical records before meeting the participants. Nevertheless, face to face consultations with the study pharmacists will capture rich data on participants’ medical history, medication lists, and their beliefs about their medications.

The deprescribing medication review will involve the following:
Pharmacist review of medication useParticipant consultationPharmacists suggesting changes in DBI medications to GPsGP consultation with the participantsGP decision to revise or not to revise DBI medication prescriptions

All medication reviews and DBI calculations will be reviewed and verified independently by a senior pharmacist (author [name]). All suggestions developed on potential deprescribing will be peer-reviewed by another study pharmacist before sending them to the participant’s GP, with additional expertise being available from the senior pharmacist.

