#### Control arm

If allocated to the control arm, the pharmacist will conduct the medication review without discussing deprescribing options with participants. The control group participants will continue to receive routine care from their GP.

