#### Six months of follow-up

For all participants, the medication use will be recorded before randomization and repeated at least 6 months later. At a 6-month follow-up, research pharmacists will revisit participants and ascertain medication usage in both study arms using the same processes as the baseline review. To avoid bias and achieve blinding of the visiting pharmacist, each participant will be visited by a different pharmacist at follow-up than the one who saw them at baseline. The post-intervention medication review will be provided to the participants’ GP for information purposes only.

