#### Access to data

The study data manager will have full unrestricted access to all study data throughout the trial. The study administrator and study pharmacists will have access to personal details to facilitate recruitment, consenting, and booking visits to participants. No other member of the research team will have access to personal details of study prospects or study participants. The senior pharmacist will have restricted access to data as required to perform data review duties throughout the trial. As a member of the Data Monitoring Group, the study statistician will have access to raw data held in REDCap to perform data quality checks. Blinding will be maintained throughout the trial.

After completing the trial and locking of data, the primary investigator and other named members of the research team will have access to de-identified study data. Data will not be shared with other researchers as per ethics approval and participant consent.

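### Participant and statistician blinding are claimed but contradicted elsewhere in the protocol, and blinding of the six-month assessor is required but not secured

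*Protocol article*

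**What the plan says.** All references are to the protocol article.

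- **Participants.** Blinding: "Participants will be blinded to their study arm". Intervention arm: the pharmacist discusses the DBI medicines with the participant, and "preferences regarding willingness to discontinue these medications will also be determined via the consultation". The listed process then includes a GP consultation. Control arm: "the pharmacist will conduct the medication review without discussing deprescribing options with participants".
- **Statistician.** Blinding: "The primary investigator and the study statistician will be blinded to participant data and allocation during the trial", with unblinding after verification and locking. Access to data: "the study statistician will have access to raw data held in REDCap to perform data quality checks". The latter section adds a general assurance that blinding is kept throughout, without saying how.
- **T2 pharmacist.** Blinding requires pharmacists doing the post-intervention reviews not to know the allocation. Six months of follow-up gives the means: "each participant will be visited by a different pharmacist at follow-up than the one who saw them at baseline". Intervention arm: "All suggestions developed on potential deprescribing will be peer-reviewed by another study pharmacist" before they go to the GP.
- **Senior pharmacist.** Intervention arm: "All medication reviews and DBI calculations will be reviewed and verified independently by a senior pharmacist". The same section makes this person's expertise available when suggestions are developed. Data entry and quality checks says that records are locked after this review or after errors are corrected. The Blinding section does not mention this role.

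**The concern.** The primary outcome is the change in DBI. It is built from a pharmacist's record of what each participant takes and how much, obtained by asking and by looking at the medicines in the home. Under a later amendment (Ethics and protocol changes) the second review could be done by telephone during the COVID-19 lockdown, and then the pharmacist cannot look. Entries for as-needed medicines require later harmonisation (Data entry and quality checks). The result is then cut at a change of 0.5 for the planned comparison of proportions.

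With an outcome recorded in this way, it matters who knows the arm. If the participant knows, the T2 pharmacist can be told. If the T2 pharmacist or the verifier has already seen that participant's recommendations, they know what change to expect. If the statistician can read intervention-only notes before lock, data-cleaning decisions are not made blind. A trial report that repeats the Blinding section would claim protection that the described procedures do not give.

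**Working it through.** The plan gives no figure for blinding, so the check is a comparison of sections.

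1. **Participants.** The Blinding claim is unqualified. Against it:
   - Intervention arm: discussion of the target medicines, their harms and benefits, the views of participant and family on continued need, and willingness to stop; then a GP consultation.
   - Control arm: a medication review with no such discussion, and routine GP care.
   - Clinical responsibility: participants are told what to do if unwell while a drug is being withdrawn.
   - Recruitment: the study is explained in detail before consent.

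   The article describes no sham discussion for controls. The intervention is itself a conversation with the participant about stopping medicines, so it cannot be delivered without the participant noticing. The claim and the procedure are incompatible.

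2. **Statistician.** Blinding covers two things, participant data and allocation.
   - *Participant data:* access to raw REDCap records contradicts this directly.
   - *Allocation:* the conflict is indirect. Outcome data lists, among the data classes, notes that support the pharmacists' deprescribing reviews. Such notes arise in the intervention arm, so seeing them would reveal the arm even if the randomization list stays hidden. The document does not say that these fields are masked for the statistician.

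3. **T2 pharmacist.** Three pharmacist functions matter for one participant: baseline visitor (B), peer reviewer of the suggestions (P) and T2 visitor (V).
   - The Intervention arm section makes P a different person from B.
   - Six months of follow-up makes V a different person from B.
   - Nothing states that V differs from P.

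   V = P satisfies every stated assignment rule. Suggestions exist only in the intervention arm, so P knows that the participant is in it. The requirement in Blinding would then be broken without any assignment rule being broken. By step 1, V can also learn the arm from the participant.

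4. **Senior pharmacist.** The word *all*, together with review before locking, indicates that T2 DBI is verified by this role. Involvement in the suggestions is possible, because expertise is available on request, but it is not stated for every case. Access to data restricts the role's access to what its review duties need, and does not say that baseline recommendations are hidden at T2. The supported statement is that this person *may* have seen the recommendations.

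5. **Scale of the outcome, not an estimate of bias.** Power and sample size plans 4% against 14% with 167 per arm. The target difference is 0.10 × 167 = 16.7, about 17 participants in one arm. One reclassified participant moves that arm's proportion by 1/167 = 0.6 percentage points. The document gives nothing from which to say how many, if any, would be reclassified.

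**The case against.** - **The T2 pharmacist is required to be blinded.** Read as a rule, the Blinding section already excludes a peer reviewer who knows the case, and an article may leave visit assignment to the full protocol. This stands in part. A reader might infer that T2 blinding is impossible or that peer reviewers will do T2 visits. The document supports neither. What remains is that the one safeguard it states is not sufficient for the requirement it states.
- **The senior pharmacist.** A reader might infer that T2 DBI is verified by someone who knows the recommendations. That is not stated: advice is only available, access is restricted, and no blinding is claimed for this role, so there is no contradiction. This stands. The point is only a possible route for knowledge of the arm.
- **Participants might not recognise their arm.** Both arms get a home visit and a review, and the information sheets are not shown. It is therefore too strong to say that every participant knows. Even so, the described difference between arms cannot support a flat claim of blinding.
- **Allocation and the statistician.** The general assurance in Access to data and the restricted randomization list speak against deliberate disclosure. They do not reconcile raw-data access with blinding to participant data.
- **Size.** It is tempting to assume that some percentage of participants cross the 0.5 line and to call it a share of the 10-point target. Such a share only restates the assumption. Looking at medicines in person limits error, a change of 0.5 corresponds to one contributing medicine at its minimum effective dose, and dispensing records are in the dataset and could serve as a check.

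**Conclusion.** The point holds at different strengths. Firm: participant blinding is claimed but is not a property of this design, and the statistician's blinding to participant data contradicts the access granted. Less firm: blinding of the T2 pharmacist is required but not secured, because the peer reviewer is not excluded and participants can reveal their arm. By inference only: the statistician could learn allocation from the notes, and the senior pharmacist may have seen the recommendations.

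This rests on two assumptions: that the deprescribing notes are kept in REDCap without masking, and that senior verification extends to T2 records. The size and even the presence of bias in the primary outcome cannot be derived from the document. Lack of participant blinding is inherent in this intervention and is no fault in itself; the fault is claiming otherwise. The plan should be corrected, but nothing here shows that the trial's result would be invalid.

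**What to change.** 1. State in Blinding that participants are not blinded.
2. Require that the T2 pharmacist be neither the baseline pharmacist nor the peer reviewer for that participant, and record at each T2 visit whether the arm became known.
3. Hide baseline recommendations and allocation from whoever verifies the T2 DBI.
4. Until lock, give the statistician only data without allocation or intervention notes, and reword Access to data and Blinding so that they agree.
5. Trial status expected recruitment to end on October 31, 2020 and data capture on May 31, 2021, so many T2 visits may be past. For those, report who assessed each one and whether that person had peer-reviewed the case.

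Cost: a visit-assignment rule, changed REDCap user rights, one extra item on the T2 form, and slightly tighter scheduling of existing pharmacists. The number of study pharmacists is not given, so how tight the scheduling becomes cannot be judged from the document. Items 1 and 5, and the rewording in item 4, need text and reporting only.
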